## Abstract

**Background:**

Cardiovascular diseases comprise a range of conditions affecting the heart and blood vessels, with numerous underlying modifiable determinants that raise the risk of heart disease, stroke, and peripheral vascular disease. Many of these risk factors could be mitigated through community-based health improvement interventions, which include physiological assessments, health behaviour coaching, psychosocial factors, and wider determinants of health support. Despite their potential, such interventions are seldom integrated into standard secondary care provision. This feasibility study aims to assess the feasibility and acceptability of the equality health-cardiovascular disease (Equality Health-CVD) intervention, a 12-week, place-based intervention for patients with vascular disease.

**Methods:**

The study will use a single-arm 12-week pilot study based in Wales, UK. A total of 20 participants will be recruited. Quantitative data (questionnaire and physical health assessments) will be collected at week 1 (baseline) and week 12. Questionnaires will include PROMIS 10, South Wales Social Wellbeing Scale and EuroQol-5D tools. Health assessments will collect data on body mass index, waist circumference, heart rate and blood pressure. One-to-one interviews will be conducted with a sub-sample of participants (*n* = 10–15) and intervention deliverers (*n* = 2). Data on participant recruitment and retention and the fidelity of intervention implementation will also be collected.

**Discussion:**

This study will provide important findings on the feasibility and acceptability of the Equality Health-CVD. Findings are critical for guiding future directions on intervention implementation and efficacy.

**Trial registration:**

ISRCTN11889657.

## Introduction and background

Cardiovascular disease (CVD), stroke and peripheral vascular disease (PVD) represent leading causes of mortality and morbidity globally, contributing to an estimated annual societal expenditure of £60 billion in the United Kingdom alone [1–5]. While these conditions impact people of all socioeconomic backgrounds, health inequalities are particularly pronounced among populations experiencing deprivation, with poorer outcomes driven by social determinants of health (SDoH) [6–8].

Stroke, transient ischemic attack (TIA), and PVD share common modifiable risk factors including atrial fibrillation, hypertension, dyslipidaemia, smoking, and diabetes [9, 10]. PVD is the third most common cause of atherosclerotic morbidity following CVD and stroke and further complicates the burden of vascular conditions [11], with patients diagnosed with PVD facing significantly greater risk of experiencing more severe cardiovascular events [12].

Preventative strategies, targeting lifestyle changes and risk factor management, can reduce recurrent vascular events; however, their success is often constrained by socioeconomic barriers [13–17].

As [name] Marmot articulates: “Why treat people and send them back to the conditions that made them sick?” p4 [18], emphasising that clinical treatment without addressing underlying social determinants perpetuates health inequalities. Despite progress in health policy recognising the influence of social gradient and social determinants of health (SDoH) on health outcomes [19, 20], achieving equitable improvements across all social gradients remains slow [21, 22].

### The evidence gap

The burden of CVD, stroke and PVD on patients, caregivers, the health system, and the broader economy is substantial, leading to reduced quality of life, high rates of hospitalisations, increased healthcare costs, and premature mortality [23, 24]. While the National Health Service (NHS) implements interventions promoting lifestyle modifications and risk management [25], there is a notable gap in research focusing on interventions that effectively address adverse SDoH, such as food and housing insecurity, violence, and poverty [26–28]. Although research has begun to explore the NHS's efforts to address inequalities [29, 30] and evidence demonstrates benefits of addressing social determinants of health [31, 32], comprehensive research on interventions that bring about significant change particularly in secondary care using place-based approaches remains limited.

Critically, no existing secondary care intervention integrates all four dimensions recommended by the adapted Labonte model [33]: (1) physiological impacts (health monitoring), (2) health behaviours (coaching and goal setting using what matters conversation), (3) psychosocial factors, (social support and connection), and (4) wider determinants of health (practical support addressing structural barriers). The National Institute for Health and Care Excellence [34] specifically recommends adopting place-based approaches integrating these dimensions to reduce health inequalities. National public bodies emphasise collaborative strategies to improve population health [35], and the NHS is uniquely positioned to address SDoH, a role intently endorsed across the UK’s four devolved nations [35, 36].

### Study rationale and novelty

This feasibility study addresses this evidence gap by testing the Equality Health-CVD intervention, a novel 12-week, home-based intervention operationalising all four Labonte model dimensions for patients with stroke (NIHSS < 5), TIA, or PVD. The intervention’s novelty lies in:Integrated multi-component design: combining health checks, personalised coaching, psychosocial support, and practical service navigation within a single coherent framework.Place-based delivery: home-based visits enabling environment assessment and addressing practical barriers inaccessible through clinic-based care, with telephone or NHS site flexibility alternatives available when preferred by participants.Secondary care timing and delivery: delivered through hospital pathways during active engagement with vascular services. For stroke/TIA patients, intervention capitalises on the critical early secondary prevention window when recurrence risk and motivation are highest. For PVD patients, intervention provides support during ongoing disease management regardless of time since diagnosis.Equality health advisors: dedicated public health professionals trained in health coaching, community asset navigation, and SDoH assessment, a distinct role from existing clinical teams.

This single-arm study was designed using the 33-item SPIRIT checklist [37] and the Medical Research Council’s framework for developing complex interventions [38].

Findings will directly inform decisions about progression to efficacy evaluation and guide optimisation of intervention design, recruitment strategies and delivery protocols (Table 1).

**Table 1 Tab1:** SPIRIT: overview of Equality Health-CVD

	Study period					
	Enrolment	Intervention				End of study
Timepoint	T0	T1	T2	T3	T4	T5
Enrolment						
Eligibility screen	X					
Informed Consent	X					
Intervention						
Equality Health Home Visit Form		X	X	X	X	
Reflective diary		X	X	X	X	
Assessments: Case Report Form A (incl. AUDIT-C)₁ Health Check (Weight, HR, BP, BMI, Waist Circumference)^2^ EQ-5D₃ PROMIS-10₄ Social Wellbeing Scale₅ Case Report Form B (incl. AUDIT-C)₆	X X X X	X			X X X X X	
Semi-structured interview						
Participants ₇					X	
Equality Health Advisor₈						X

*SPIRIT*: overview of Equality Health-CVD. Subscript digit one (1) indicates the following: At baseline, socio-demographic information will be collected, including age, gender, ethnicity, living arrangements, pain level, smoking status and Audit C, Alcohol Use Disorders Identification Test.; superscript two (2) indicates the following: physical testing assessments to identify health risk factors and health status; subscript digit three (3) indicates European Quality of Life 5 Dimension Level 5; subscript digit four (4) indicates the following: PROMIS-10, Patient-Reported Outcomes Measurement Information System Global Health; subscript digit five (5) indicates the following: The South Wales Social Wellbeing Scale (SWSWBS); subscript t digit six (6) indicates the following: End of intervention evaluation items and Audit C, Alcohol Use Disorders Identification Test; subscript digit seven (7) indicates the following: participants semi structured interview questions that will be completed at the final follow up visit; subscript digit eight (8) indicates the following: Equality Health Advisor semi structured interview questions that will be completed at the end of the study

### Feasibility study aims

Before progressing to a full-scale effectiveness trial, this feasibility study will:Assess whether the intervention can achieve adequate recruitment and retention in this population? (RQ1).Determine whether the intervention can be delivered with fidelity and data collection is feasible (RQ2)Examine intervention acceptability to participants using Theoretical Framework of Acceptability (RQ3)Explore deliverers’ perspectives on implementation feasibility, identifying barriers, facilitators and refinement needs (RQ4).

### Study design

This feasibility study is a UK-based single-site pilot study of the Equality Health–CVD intervention. The intervention consists of four home visits encompassing health checks, coaching, support linked to social connections and wider determinants of health delivered by Equality Health Advisors over a 12-week period. Tables 2 and 3 logic model articulates the conceptual framework of the Equality Health–CVD intervention including how the context, intervention activities interlink with perceived impact and outcomes.

**Table 2 Tab2:** Equality Health-CVD logic model

Context	Intervention	Mechanisms of impact	Intervention outcomes
Setting: Secondary care support service. Target population: People diagnosed with either of the following: • History of ischemic stroke NIHSS score of less than 5 • History of Transient ischemic attack • Peripheral Vascular Disease Number of Participants Total = 20 Aim: Improve Health and Wellbeing Age: Male and Female – Age 18 to 100 Deliverers: Equality Health Advisors Number of Visits: 4 visit in total – approximately 4 week apart Length of Visit: Approximately 1 hour	Link participants to community-based interventions Link participants to CIVIC interventions that support (Closeness, Identity, Valued relationships, Involvement, Cared for/accepted) – Civic duty Provide Health and Wellbeing coaching using basis CBT (Using NHS England health and wellbeing coaches framework) Physiological testing • Blood Pressure and HR • Height • Weight • BMI • Waist Circumference Act upon wider determinants of health Fuel poverty -Nest Income – Citizens Advice Poor housing and living conditions. Education Unemployment Health care service	Accessible pathways into service-based and community-based interventions Participative social functioning Knowing who to contact Participant is Listened to Supporting Participant motivation Flexible role Trusting interpersonal relationship Person-centred approach Adaptability of intervention Cross pathway referrals	Improved physical health Improved mental health and well-being Better Health Behaviours Increased social connectedness Reduce social isolation. Improved healthcare utilisation outcomes (such as fewer GP visits and lower emergency admission) Increase Self Efficacy in managing personal health Enhance goal achievement Reduction in risky health behaviours Improve health literacy Support health awareness through physiological testing Increased engagement in preventive health behaviours Improve disease management Greater awareness of social determinants of health Increase access to essential services (e.g., healthcare, transportation)

**Table 3 Tab3:** Key components in the Equality Health Advisor Handbook

Key components
Quality standards
Health check guidance
Health coaching guidance
Psycho-social wellbeing guidance
Wider determinants of health guidance
Documentation and follow-up
Escalation process

## Recruitment and study setting

### Sociodemographic context of recruitment area

The study will recruit from hospital sites across the Aneurin Bevan University Health Board (ABUHB) catchment area, serving a population of approximately 565,412 people across five local authorities in Gwent, South Wales: Blaenau Gwent, Caerphilly, Monmouthshire, Newport, and Torfaen [39].

This area demonstrates substantial socioeconomic heterogeneity with significant pockets of deprivation. According to the Welsh Index of Multiple Deprivation (2025) [40]:Blaenau Gwent ranks as one of the most deprived local authorities in Wales, with the highest proportion of small areas in the most deprived 10% in Wales (20% representing 9 areas), followed by Newport (18% or 18 areas).Torfaen also shows significant deprivation, with (8.3%) of LSOAs falling within the most deprived 10% of LSOAs.Caerphilly demonstrates a mixed deprivation pattern, with former coalfield communities experiencing pockets of deep-rooted deprivation.Monmouthshire is relatively affluent but contains pockets of rural deprivation.

These deprivation patterns translate into substantial health inequalities. Data from the Gwent Joint Strategic Assessment 2024/25 [39] reveal:Female life expectancy in Gwent is 81.3 years, but healthy life expectancy is 57.9 years, meaning women could live up to 23.4 years in ill health.Torfaen shows the lowest healthy life expectancy for women at 53.3 years, 4.6 years below the Gwent average, indicating particularly pronounced health inequalities.Male life expectancy in Blaenau Gwent is 76 years (2 years below the Welsh national average); however, men spend an average of 19.3 years in ill health.Age standardised premature death rates from key non-communicable diseases that include stroke, TIA, PVD, cancer, diabetes and respiratory conditions between are 279.6 per 100,000 for women and 383.6 per 100,000 for men (2021–2023)

The social diversity of the ABUHB catchment area provides opportunity to recruit participants experiencing significant SDoH challenges. Hospital and clinic-based recruitment through secondary care pathways provides access to patients from across this diverse socioeconomic spectrum (Fig. 1).

**Fig. 1 Fig1:**
[figure not shown]
Participant timeline and study flow chart

#### Participants

The study aims to recruit 20 participants between October 2024 and August 2025. Participants in the study will undergo eligibility screening in various hospital sites across the Aneurin Bevan University Health Board. Recruitment will be achieved by approaching all appropriate outpatient clinics. Eligible participants will be provided with verbal information about the study and given a copy of a patient information sheet by the Aneurin Bevan University Research Team. Participants will be given adequate time to review the information sheet and ask questions. Participants may choose to give consent on the same day or take the information home to consider. In this case, patients will have the option to be contacted by the research team or given the contact details of the research team to arrange a follow-up appointment. Consented participants will self-complete Case Report Form A, which includes demographic and SDoH profile data collection (housing, income, social support, service access barriers) and various validated social and wellbeing patient-reported outcome measures. Thereafter, participants will be offered the first Equality Health appointment at a convenient time for the participant.

Potentially eligible participants will reside in Gwent, where identification, screening, and consent will take place at various sites across Aneurin Bevan University Health Board in Wales during a routine outpatient appointment or as an inpatient.

#### Study population: inclusion and exclusion criteria

This feasibility study deliberately includes patients with three related vascular conditions: a history of ischaemic stroke, National Institutes of Health Stroke Scale (NIHSS) score of less than 5, a history of transient ischaemic attack (TIA), or a referral to a Peripheral Vascular Clinic. This heterogeneous approach is justified on theoretical and pragmatic grounds. All three conditions result from atherosclerotic vascular disease sharing common mechanisms and modifiable risk factors [9–12]. Additionally, the Equality Health-CVD intervention targets the person and their environment, not the specific vascular pathology. Heterogeneity will be mitigated through baseline characteristics reported by condition subgroup, recruitment/retention rates analysed by pathway and qualitative interviews will be examined for any emerging diagnosis-specific themes that may inform future trial design.

Participants eligible for recruitment in this study are those aged 18 years or older. Eligible participants must also have the capacity to provide informed consent and express a willingness to participate in a qualitative interview at the conclusion of the intervention. Exclusion criteria include patients receiving or eligible for palliative care. Unwillingness or inability (e.g. physical or cognitive) to comply with study procedures. Patients already participating in a clinical rehabilitation home intervention and with an unwillingness to take part in a qualitative interview at the end of the intervention are also excluded.

#### Sample size

The sample size of 20 participants is appropriate for a feasibility study and aligns with published guidance on feasibility trial design [41–43]. The participants will be selected through convenience sampling; this decision was made due to time and resource constraints [44]. The study will remain open for 12 months. Recruitment progress will be closely monitored, and strategies will be adapted as needed to ensure target enrolment is achieved. The study will remain open until October 2025, at which point it will close for data analysis.

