In addition, the Equality Health Advisors will also participate in semi-structured interviews to explore their views of the Equality Health-CVD study using a similar thematic qualitative approach.

During the development of the protocol, the lead researcher conducted a public and community asset mapping exercise to identify services, activities, and local contacts available across the five local authorities in Gwent. All information was added to templates with the aim to help the Equality Health Advisors to navigate public and community asset provision.

A series of patient and professional consultations were organised to inform the co-design of the protocol and intervention. To support the intervention, health check equipment was purchased, and an Equality Health Adviser Handbook was created. This handbook aims to provide a framework for delivering the Equality Health-CVD intervention focusing on four dimensions of the adapted Labonte model (Table 4).

**Table 4 Tab4:** Intervention procedures

Procedure	Timepoints (Weeks)
Eligibility criteria review	Week 0
Informed consent	Week 0
Medical history	Week 0
Case Report Form A (incl. AUDIT-C)	Week 0
Health Check (Weight, HR, BP, BMI, Waist Circumference)	Weeks 1 and 12
EQ-5D	Weeks 0 and 12
PROMIS-10	Weeks 0 and 12
South Wales Social Wellbeing Scale	Weeks 0 and 12
Equality Health Home Visit	Weeks 1, 4, 8, 12
Case Report Form B (incl. AUDIT-C)	Week 12
Semi-structured interview	Week 12

The Equality Health Advisors are employed by the Aneurin Bevan University Health Board within the Public Health Team. Prior to study implementation, the Equality Health Advisors received additional training to support safe and effective communication with participants, which included a health coaching course, first aid emergency responder, and various online courses in clinical skills, service navigation, and community engagement.

To balance protocol fidelity with real-world feasibility, consultations may be scheduled within a ±14-day window around target dates.Consultation 2: target week 4 (deliverable weeks 2–6)Consultation 3: target week 8 (deliverable weeks 6–10)Consultation 4: target week 12 (deliverable weeks 10–14)

This flexibility reduces unnecessary barriers to participation, including work schedules, caregiving responsibilities, health fluctuations, or any additional challenges that may arise (Table 4).

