### Outcomes

#### Primary

The primary outcome is to evaluate the feasibility and acceptability of the Equality Health–CVD study in terms of recruitment and retention rate to the intervention (Study objective 1). A record will be kept of the number of participants recruited within 9 months of the study opening, including the number of participants who participated in the 12-week follow-up. Additionally, a feasibility assessment of intervention fidelity will be conducted (Study objective 2). This will involve documenting the number of home visits completed, recording the data collected during each visit, and tracking the outcomes of signposting to community and public assets.

Secondary outcomes: the secondary outcomes will examine the experiences and acceptability of the intervention from the perspectives of both participants and deliverers (Equality Health Advisors). This evaluation linked to (objective 3 and 4) will include identifying barriers and facilitators to delivery as well as perceived impacts. Data will be collected through qualitative semi-structured interviews conducted at the end of the intervention for participants and at the end of the study for Equality Health Advisors. To complement these findings, reflective diaries maintained by Equality Health Advisors during home visits will also be analysed.

In addition, participants will complete a series of validated questionnaires at baseline and 12 weeks post-baseline as part of the feasibility study's evaluation. These quantitative Patient-Reported Outcome Measures (PROMs) will be used in conjunction with qualitative semi-structured interviews as data descriptors. This will facilitate whether the participants are willing and able to complete these measures, in addition to capturing subjective health and social wellbeing outcomes that may enhance data richness.

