**Table Taba:** 

Linked RQ	Progression criteria		Green light	Amber light	Red light	Data
	N	Detail				
1. Recruitment	1	% of target number of participants recruited (target: 20; 9 -month recruitment period)	>75%	60–75%	< 60%	*Screening log* *Baseline, RN – Informed Consent Form CRF A*
1. Retention	2	% of patients who participate in 12-week follow-up (of those who complete min. 1 intervention session)	>65%	50–65%	<50%	12-week follow up questionnaire
2. Feasibility of intervention implementation	3	The intervention is implemented with fidelity (i.e., 4 home visits conducted with data collected recorded at each visit and signposting to community and public assets)	No traffic light criteria to be applied			HEA reflective diaries 12-week interview data
3. Acceptability of the intervention	4	Data indicates the intervention is acceptable to participants and deliverers				HEA reflective diaries 12 week interview data

The Green light system (progression criteria) indicators are as follows:Green—indicates current procedure can be used for future studyAmber—indicates current procedure needs attention with discussion for optimisation in future studyRed—indicates current procedure is unacceptable and not feasible therefore an alternative will need to be tested within a future study

The Study Management Group (SMG), which includes an ABUHB Quality Assurance Officer, an Independent Data Validation Reviewer (Quantitative), and an Independent Data Validation Reviewer (Qualitative), will review all aspects of the progression criteria.

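### The recruitment end date (August 2025, or nine months) is not reconciled with closure for analysis in October 2025, so late enrolees may miss the 12-week follow-up on which retention is judged

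*Protocol article*

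**What the plan says.** All of these statements are in the Protocol article.

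- Participants: "The study aims to recruit 20 participants between October 2024 and August 2025". The first appointment follows consent at a time that suits the participant, with no upper limit given there. Table 4 places it at week 1.
- Sample size: "The study will remain open for 12 months", and then "The study will remain open until October 2025, at which point it will close for data analysis".
- Equality Health-CVD intervention: "consultations may be scheduled within a ±14-day window around target dates". For the last visit this gives "Consultation 4: target week 12 (deliverable weeks 10–14").
- Outcomes, Primary: "A record will be kept of the number of participants recruited within 9 months of the study opening", together with the number taking part in the 12-week follow-up.
- Progression criteria table: recruitment is the percentage "of target number of participants recruited (target: 20; 9 -month recruitment period"). Retention is the percentage "of patients who participate in 12-week follow-up (of those who complete min. 1 intervention session"), with green above 65%, amber 50 to 65% and red below 50%.

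**The concern.** The document gives two recruitment end points. August 2025 is 10 to 11 months after an October 2024 start, whereas the primary outcome and the recruitment criterion stop at nine months. Only the nine-month version leaves room for a 12-week follow-up before October 2025.

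Retention at 12 weeks is part of the primary outcome and one of only two criteria with a traffic-light threshold. A participant who enrols too late to be seen before closure has not dropped out, but cannot supply the follow-up that the criterion counts. The same person would also lose the fourth session, the second health check, Case Report Form B, the week-12 questionnaires and any interview. The fourth visit also belongs to the fidelity criterion.

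**Working it through.** **Inputs.** Recruitment from October 2024 to August 2025 (Participants); 12 months open and closure in October 2025 (Sample size); final visit at week 12, window weeks 10 to 14 (Equality Health-CVD intervention); nine-month recruitment, target 20 and the retention ratio (Primary; progression criteria table). Three assumptions are needed. Weeks are counted from consent as week 0, as in Table 4. The closure day is not given, so 1 to 31 October is tested. The opening day is not given and is taken as 1 October 2024 unless stated.

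**Step 1: the plan's own figure.** October 2024 plus 12 months is October 2025, as stated.

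**Step 2: the nine-month version.** Nine months from 1 October 2024 ends on 30 June 2025. Adding 12 weeks gives 22 September and adding 14 weeks gives 6 October. Week 12 fits any October closure, and the full window fits unless closure falls in the first days of October. The margin is thin: 30 June to 30 September is 92 days, while 14 weeks is 98 days, so nine months plus the full window exceeds an exact 12 months by 6 days. Opening on 31 October 2024 gives the same result one month later: recruitment to 31 July 2025, week 12 on 23 October, week 14 on 6 November.

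**Step 3: the August version.**

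| Enrolled | Week 10 | Week 12 | Week 14 |
|---|---|---|---|
| 1 Aug 2025 | 10 Oct | 24 Oct | 7 Nov |
| 15 Aug 2025 | 24 Oct | 7 Nov | 21 Nov |
| 31 Aug 2025 | 9 Nov | 23 Nov | 7 Dec |

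Even 31 October is only 61 days (8.7 weeks) after 31 August.

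**Step 4: last workable enrolment date** (closure date minus 10, 12 or 14 weeks).

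| Closure | Any in-window visit (week 10) | Week 12 | Full window (week 14) |
|---|---|---|---|
| 1 Oct 2025 | 23 Jul | 9 Jul | 25 Jun |
| 15 Oct 2025 | 6 Aug | 23 Jul | 9 Jul |
| 31 Oct 2025 | 22 Aug | 8 Aug | 25 Jul |

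**Step 5: participants affected.** This assumes even accrual of 20 over the 335 days from 1 October 2024 to 31 August 2025. Expected number = 20 × (days from the limit to 31 August) / 335.

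- No in-window visit possible: 20 × 9/335 = 0.5 (closure 31 October) to 20 × 39/335 = 2.3 (closure 1 October).
- Week 12 not reachable: 20 × 23/335 = 1.4 to 20 × 53/335 = 3.2.
- Full window not available: 20 × 37/335 = 2.2 to 20 × 67/335 = 4.0. This group includes people who can still be seen by week 12.

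**Step 6: effect on the retention light.** Suppose all 20 have at least one session. Since 13/20 is exactly 65%, green needs 14/20 (70%). If two who would have been retained are cut off and stay in the denominator, 14/20 becomes 12/20 = 60%, amber. If they are left out of the denominator, it is 12/18 = 66.7%, green. At an assumed true retention of 75%, with m participants cut off and kept in the denominator, the chance of green is P(X ≥ 14) for X ~ Binomial(20 − m, 0.75): 0.79 for m = 0, 0.67 for m = 1, 0.52 for m = 2 and 0.35 for m = 3.

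**The case against.** The strongest reply is that the recruitment definition tied to the primary outcome is nine months, and that this largely fits an October closure. On that view only the August date is out of line, and if the target is met within nine months nobody enrols late. This is right as far as it goes, and it rules out reading the follow-up schedule as unworkable. It does not remove the conflict, because the Participants section still permits enrolment to August.

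A reader might also infer that cut-off participants will be scored as not retained. The documents do not say so. They give a ratio but no rule for participants still in follow-up at closure. They do not say that follow-up stops mid-intervention, and late enrolees with no session leave the denominator. Such a rule may stand in a full protocol or analysis plan that is not shown, so its absence is no finding. What stands is the literal effect of the ratio.

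Nor is a loss of up to four participants supported. That figure counts everyone without the full 14-week window, although some of them can be seen at week 10 to 12.

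The move from 14/20 to 12/20 is a borderline illustration. It starts at the lowest green count and takes both cut-off participants to be people who would have stayed; from 16/20 the same loss leaves 14/20, still green. Finally, amber only calls for discussion and optimisation, the Study Management Group reviews all the criteria, and the article claims no effectiveness inference.

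**Conclusion.** The point holds as an inconsistency of dates with a moderate consequence. Recruitment through the end of August 2025, a final visit in weeks 10 to 14 and closure for analysis in October 2025 cannot all be met, whichever day in October is meant. If August meant only its first week and closure were 31 October, all would reach week 12, but the week-14 limit would still overrun.

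Under even accrual to 31 August, about 1.4 to 3.2 of 20 could not reach week 12, and about 0.5 to 2.3 could have no in-window final visit. Even accrual is an assumption. Slower early recruitment would raise these numbers, and filling the 20 places within nine months would bring them to few or none. A long wait for the first session would worsen the fit if the schedule moves with it, but Table 4 targets week 1. The threat to the retention light is real for a result near 65% and small otherwise.

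**What to change.** Reconcile the dates in the Participants, Sample size and Primary sections and the progression criteria table, in one of two ways.

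1. End consent at the nine-month point and name a closure day at least 14 weeks plus the wait for session 1 after it. With opening on 1 October 2024, that means last consent on 30 June 2025 and closure no earlier than 6 October 2025 plus any wait. The cost is two months of possible enrolment (July and August).
2. Keep August and hold data collection open until the last participant's week-14 window ends. For enrolment to 31 August that is 7 December 2025: 37 days (5.3 weeks) after a 31 October closure, or 67 days (9.6 weeks) after a 1 October closure, plus any wait for session 1. A reader might put the extension at about six weeks at most, but that holds only for a late-October closure.

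Neither option needs extra participants. The first changes one date and names a closure day. If enrolment has already ended, report the actual last consent and closure dates, and how anyone still in follow-up at closure was counted in the retention ratio.
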